### Interventions

#### Supported Protocolized discontinuation (SPD)

Patients who choose to discontinue their medication will make a personal tapering schedule with their GP based upon a discontinuation protocol with tapering suggestions. The protocol offers suggestions to taper within a maximum of 6 months describing all types of available dosages per ADM so individualized schedules can be constructed. The protocol is available upon request through the research team (CW). In addition, they will be offered supportive meetings with the GP’s mental health assistant. The assistant will receive basic information about discontinuation guidance, i.e. the information brochure, decision aid, discontinuation protocol and a short guideline how to organise consultations. The short guideline is available upon request through the research team (CW). Patients will be advised to discontinue their medication within 6 months.

#### Mindfulness based cognitive therapy (MBCT)

MBCT will be offered according to the treatment protocol developed for recurrent depression [30], adapted to the specific needs of patients discontinuing their antidepressant medication. The psycho-education sections about depression will be extended with information about pro and cons of stopping antidepressants, withdrawal effects and anticipatory anxiety. Based on our expectation that the discontinuation process may take longer than is currently regarded as common practice, sessions 1–4 will take place on a weekly and sessions 5–8 on a fortnightly basis. Each session will last 2.5 h with a 6-h silent day between session six and seven. In addition to the group sessions, participants will be instructed to practice mindfulness for approximately 30 min a day. Participants will receive a digital link to download guided meditations and yoga exercises for home practice. The mindfulness courses will be provided by teachers qualifying the advanced criteria of the Association of Mindfulness Based Teachers in the Netherlands and Flanders, which include a) relevant professional training; b) having attended MBSR / MBCT as a participant; c) a minimum of 150 h of education in MBSR/MBCT background and theory, training in teaching formal and informal meditation practices, psycho-education and inquiry, supervision and teaching an MBSR or MBCT course including a reflection report; d) teaching a minimum of two courses per 2 year; e) minimum of 3 years of practicing meditation regularly and attending retreats; and f) continued training. All teachers will receive additional training in using the specific study protocol at the start of the project. We will organize two peer supervision meeting per course during the intervention phase of the trial. Teaching sessions will be videotaped to check treatment integrity. A random selection of two tapes per teacher will be rated for treatment adherence and competency by highly experienced MBCT/MBSR teachers with the Mindfulness-Based Cognitive Therapy Adherence Scale [31].

### Outcome measures

Table 1 presents an overview of the outcome measures and the time points of assessments.

**Table 1 Tab1:** Overview of the measures and corresponding time points

Measure	Target concept	Baseline (T0)	FU6 months (T1)	FU9 months (T2)	FU12 months (T3)
Daily calendar	Use of antidepressants	Daily registration during 12 months			
SCID I modules*	Global psychopathology	*	*	*	*
DESS	Discontinuation symptoms	*	*	*	*
IDS-C	Depressive symptoms	*	*	*	*
STAI	Anxiety trait & state	*	*	*	*
M.I.N.I. plus Suicidal	Suicide cognitions	*	*	*	*
RRS-brooding	Rumination brooding	*	*	*	*
MHC-SF	Positive mental health	*	*	*	*
FFMQ-SF	Mindfulness skills	*	*	*	*
SCS-SF	Self compassion	*	*	*	*
TIC-P	Direct and indirect costs	*	*	*	*
EQ-5D	Quality of life	*	*	*	*

Note. *Scid I modules screening, mood episodes & disorders and anxiety disorders. All questionnaires are online self-reports except SCID-I modules and IDS-C (interview) and daily calendar (pen&paper). If participants do not have internet-access paper questionnaires will be offered

#### Primary outcome measure

Our primary outcome will be full discontinuation of antidepressant medication (= 0 mg) within 6 months after starting the intervention. Use of medication will be measured with daily calendars. Patients will be invited to fill out paper calendars describing their type of antidepressant, daily milligrams used and consultations to GP or mental health assistant regarding tapering. In case of missing data in the reports, the GP will be contacted to check the GP prescription database. This latter solution is considered reliable as in the Netherlands all patients are linked to only one GP who collects all medical information for a particular patient.

#### Secondary outcome measure

*Relapse/recurrence in depression and/or anxiety* will be measured by the modules ‘screening, mood episodes & disorders and anxiety disorders’ of the Structural Clinical Interview for DSM-IV Axis I Disorders (SCID-I), as the SCID-I for DSM-V was not available at the start of the project. Interviews will be conducted by qualified research assistants who received one full day of training to use the SCID-I. Interviews will be audio taped to allow second-rating by an independent and blind assessor in a random sample of tapes in order to prevent bias. Previous studies on inter-rater reliability of the SCID-I have reported Cronbach’s alpha values between 0.61 and 0.80 [32]*Withdrawal symptoms* will be assessed by means of the Discontinuation-Emergent Signs and Symptoms, DESS. This self-report will be administered to all patients using either SSRI, SNRI, TCA or other antidepressant medication. The checklist consists of 43 items and is based on an evaluation of signs and symptoms associated with discontinuation or interruption of SSRI treatment, as reported in the available literature [33]. A Dutch translation of DESS by Grootheest will be used.*Depressive symptoms* will be measured by the Inventory for Depressive Symptoms, IDS-C. The 30-item interview is designed to assess the severity of depressive symptoms. In this study we use the clinician rated version. The IDS-C has good psychometric qualities [34, 35].*Suicide cognitions* will be measured by the module Suicide Cognitions of the Mini International Neuropsychiatric Interview, MINI. The 6-item interview is designed to assess suicidal cognitions over the last month and to specify suicidal risk. In this study we use the clinician rated version [36].*Anxiety symptoms* will be measured by the State-Trait Anxiety Inventory, STAI [37]. A self-report measure which has been proven reliable and sensitive in the assessment of both state and trait levels of anxiety. It is a standard international measure in anxiety research and its Dutch translation has been validated [38].*Ruminative Brooding* will be measured by the brooding subscale of the extended version of the Ruminative Response Scale (RRS-EXT) which consists of 5 items. The authors reported adequate internal consistency *α* = .79 and test–retest stability (*α* = .62, 1 year time interval) [39].*Positive mental health* will be assessed with the 14-item Dutch short-form version of the Mental Health Continuum, MHC-SF [40]. The self-report questionnaire assesses emotional, psychological and social well-being. It has adequate psychometric qualities in terms of good internal consistency, (moderate) test-retest reliability, and good divergent and convergent validity.*Mindfulness skills* will be assessed with the Dutch short form of the Five Facet Mindfulness Questionnaire, FFMQ-SF [41]. This is a self-report inventory that specifies five mindfulness skills: observing, describing, acting with awareness, non-judging and non-reactivity. It consists of 24 items. The FFMQ has demonstrated to be a reliable and valid measure in assessing mindfulness in people with depressive symptoms.*Self-compassion* will be measured with the 12-item Dutch short-form version of the Self-Compassion Scale, SCS-SF [42]. The scale consists of six components: self-kindness, self-judgment, common humanity, isolation, mindfulness and over-identification. The SCS-SF has good reliability and validity.

#### Cost-effectiveness

*Resource use* such as use of care, medication and illness related to work will be measured by means of the TIC-P. The TIC-P is a self-report inventory that consists of 38 items and measures both direct costs, i.e. care consumption of people suffering from psychiatric illness, and indirect costs, i.e. costs associated with production loss over the 12 month follow up period [43].To evaluate *quality of life* the EuroQol-5D, self-report version, will be used [44]. The EQ-5D uses a descriptive system of health-related quality of life states consisting of five dimensions (mobility, self-care, usual activities, pain/discomfort and anxiety/depression) each of which can take one of three responses. In addition it contains a visual analogue scale to determine Quality Adjusted Life years (QALYs). The Dutch translation will be used.

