### Secondary analyses

We will use Cox regression analysis for differences in time to relapse/recurrence in depression and/or anxiety and multilevel regression analysis for all other secondary outcomes. Baseline scores of all continuous variables will be included as covariates in the respective analyses.

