### Cost-effectiveness evaluation

The cost-effectiveness evaluation will be carried out from both a medical and societal perspective considering direct health related costs and societal costs following the Dutch guideline [45]. Total costs, measured with the TIC-P, will be estimated using an incremental bottom-up (micro-costing) approach, where information on each element of service used is multiplied by an appropriate unit cost and summed to provide an overall total cost [46]. We will consider four types of costs: (1) intervention costs of offering the MBCT, (2) costs stemming from health care uptake related to discontinuation, (3) patients’ and their family’s out-of-pocket costs, (4) costs stemming from productivity losses due to absenteeism related to discontinuation. The recall period will be 4 weeks at baseline, and will consist of the entire period between each of the follow-up assessments. Intervention costs will include all the costs that will contribute to the development and administration of the MBCT, for example costs of training and travel expenses. Total costs for each patient will be obtained by multiplying these data with standard costs, based on the Dutch guideline for costing research [45]. Cost as outcome are mostly skewed. In our analysis we will take skewness into account by using a GLM approach with a gamma distribution and log link. Cluster effects will be accounted for by cluster robust standard errors. Descriptive statistics on costs will be presented as well. Health-related quality of life from baseline up to 12 months will be used to calculate QALYs based on the EQ-5D using the trapezium rule. Incremental cost-effectiveness will be expressed in terms of incremental costs per QALY gained. Bootstrap simulations with 1,000 replications will be used to produce uncertainty intervals in our economic evaluation, taking into account the correlations between costs and QALYs. A cost-effectiveness acceptability curve (CEAC) will be produced to show the probabilities that either of the tested strategies is the cost-effective option, given certain values for the cost-effectiveness threshold (i.e. a willingness to pay for a QALY gained). If there are baseline differences between groups a net monetary benefit and regression based framework will be used. Uncertainty surrounding non stochastic parameters (like prices) will be explored using one way sensitivity analyses.

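### The article ties QALYs to the EQ-5D visual analogue scale and adjusts for baseline only if groups differ; QALYs should come from the five-dimension profile and always be adjusted for baseline utility

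*Protocol article*

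**What the plan says.** **Source of the QALYs.** The Cost-effectiveness section, under Outcome measures, describes the EQ-5D as five dimensions, "each of which can take one of three responses". It gives the profile no role in the QALY and names no value set. The next sentence reads "In addition it contains a visual analogue scale to determine Quality Adjusted Life years (QALYs". The Cost-effectiveness evaluation section says that health-related quality of life from baseline to 12 months "will be used to calculate QALYs based on the EQ-5D using the trapezium rule". It does not say which part of the EQ-5D is meant. Table 1 has the EQ-5D at baseline and at 6, 9 and 12 months.

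**Baseline adjustment.** The evaluation section says: "If there are baseline differences between groups a net monetary benefit and regression based framework will be used". It does not define a baseline difference. For the clinical outcomes, the Secondary analyses section says: "Baseline scores of all continuous variables will be included as covariates in the respective analyses".

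**Clustering and uncertainty.** Directly after the gamma model for costs, the evaluation section says: "Cluster effects will be accounted for by cluster robust standard errors". A few sentences later it says: "Bootstrap simulations with 1,000 replications will be used to produce uncertainty intervals in our economic evaluation", "taking into account the correlations between costs and QALYs". It does not say whether GPs or patients are resampled.

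**The concern.** Cost per QALY requires a utility: a preference-based value on a scale anchored at dead and full health. The five-dimension profile yields one when scored with a value set. The VAS records how the patient rates his or her own health and is a different quantity. The only sentence that names a component of the EQ-5D as the source of QALYs names the VAS. Under the present text, two analysts could compute two different incremental QALYs from the same data, and the choice could be made after results are seen.

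Baseline utility is part of the area under the curve and also predicts later utility. If adjustment waits until a difference is noticed, the estimator depends on the data, and a gap judged too small to count is read as QALY gain or loss. The design makes this more than a matter of chance. Under Procedure, GPs are allocated and then identify and invite their patients and share the decision to taper. Under Design, patient and GP know the allocation. Baseline imbalance can therefore arise from recruitment as well.

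For the bootstrap the question is narrower. Cluster-robust standard errors for a cost model do not by themselves carry over to bootstrap intervals or to the acceptability curve.

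**Working it through.** **1. Which part of the EQ-5D gives the QALY.** No arithmetic applies. The outcome section assigns QALYs to the VAS. The evaluation section assigns them to the EQ-5D, of which the VAS and the profile are both parts. The second statement neither confirms nor corrects the first. The document gives no utility or VAS values, so the size of the difference cannot be computed.

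**2. Weight of baseline in the QALY.** Visits at 0, 6, 9 and 12 months (Table 1) give intervals of 0.5, 0.25 and 0.25 years. Under the trapezium rule each visit gets half of each adjoining interval:

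- baseline: 0.5/2 = 0.25
- 6 months: 0.5/2 + 0.25/2 = 0.375
- 9 months: 0.25/2 + 0.25/2 = 0.25
- 12 months: 0.25/2 = 0.125

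The sum is 1. Let d be the baseline gap in utility between arms and r the share of it that persists at each follow-up visit with no treatment effect. The unadjusted QALY difference then shifts by d × (0.25 + 0.75r).

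- r = 0 (direct part only): 0.25d
- r = 0.4: 0.55d
- r = 0.8: 0.85d

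The document gives neither d nor r. As an illustration, an assumed d of 0.05 gives 0.05 × 0.55 = 0.0275 to 0.05 × 0.85 = 0.0425 QALY.

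**3. How large a gap could go unadjusted.** The trigger is not stated. If it were a 5% test (assumed), gaps up to 1.96 × √(2 × DE/n) standard deviations would be left alone, where DE is the design effect.

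- n = 69 per arm, DE = 1.0: 1.96 × √(2/69) = 0.33 SD
- n = 69 × 0.85 = 58.65 per arm, DE = 1.2: 1.96 × √(2.4/58.65) = 0.40 SD

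**4. The plan's design effect, and what it implies for the bootstrap.** The Sample size section gives 15% versus 40%, 80% power, two-sided 5%, ICC 0.05, 15% dropout and 5 patients per GP. The standard two-proportion formula without continuity correction gives 49 per arm.

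- DE = 1 + (5 − 1) × 0.05 = 1.20
- 49 × 1.20 = 58.8, and 58.8/0.85 = 69.2 per arm, or 138.4 in total, against the stated 69 and 138
- 138 × 0.85/5 = 23.5, hence 24 GPs, about 12 per arm

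The plan's figures reproduce, so DE = 1.20 can be used. If patients were resampled without regard to GP, the standard error would be too small by 1 − 1/√DE, and a nominal 95% interval would cover 2Φ(1.96/√DE) − 1:

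| ICC | DE | SE too small by | Coverage |
|---|---|---|---|
| 0.01 (assumed) | 1.04 | 1.9% | 94.5% |
| 0.05 (plan, for discontinuation) | 1.20 | 8.7% | 92.6% |
| 0.10 (assumed) | 1.40 | 15.5% | 90.2% |

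The document gives no ICC for costs or QALYs, which is why a range is shown.

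**5. Resampling whole GPs is not a complete answer.** With 12 GPs per arm, the bootstrap standard error from resampling GPs is low by a factor of about √(11/12) = 0.957, or about 4%. In a simulation with normal data, 12 GPs per arm and 5 patients each, percentile intervals from this bootstrap covered about 91% to 93%.

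**The case against.** **The VAS sentence may be loose wording.** It describes the instrument and is not an analysis rule. The evaluation section says only EQ-5D and follows a Dutch guideline that is not shown. A reader might infer that the analysis will use the VAS, but the document does not prove this. The value set itself may be left to the full plan. What stands is that the article makes an affirmative statement that assigns QALYs to the wrong component, and nothing elsewhere in it corrects this.

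**Baseline adjustment is foreseen.** If a difference appears, the regression framework applies. No threshold is stated, so the document does not show that any particular gap, such as 0.05, would be left alone. The shifts above are therefore the cost of not adjusting, and not the expected cost of this plan. That is fair. It does not answer the missing criterion or the contrast with the clinical analyses.

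**The bootstrap is not said to ignore clusters.** A reader might infer that it does, because only the correlation between costs and QALYs is named. But the resampling unit is simply not given. The same section promises cluster-robust standard errors, and the Randomization and statistical analysis section commits to accounting for patients nested within GPs. An article may leave the resampling unit to the full plan. This objection largely succeeds, and only a request for clarification remains.

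**Conclusion.** The point holds in two parts, and both rest on stated text. First, the article ties QALYs to the VAS in one section and to the EQ-5D in general in another. These must be reconciled, and the numerical consequence cannot be derived from the document. Second, baseline adjustment in the economic analysis depends on an undefined baseline difference. Without adjustment, a gap d shifts the QALY difference by 0.25d directly, and by 0.55d to 0.85d in all if carry-over is 0.4 to 0.8 (assumed).

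The bootstrap is a minor clarification. If patients were resampled without regard to GP, the standard error would be about 9% too small at ICC 0.05 and 5 per GP (1.9% to 15.5% for ICC 0.01 to 0.10, assumed). That would affect the intervals and the acceptability curve, not the point estimate.

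The document does not support the stronger conclusion that the incremental QALYs and their uncertainty are wrong. As written, they are open to avoidable bias and to two readings. The economic evaluation is secondary, and the primary outcome is not affected.

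**What to change.** 1. State in both sections that QALYs are computed from the five-dimension profile, scored with a named value set, and that the VAS is reported descriptively.
2. Replace the conditional sentence. The regression (net monetary benefit) framework is used in every case, adjusted for baseline utility and baseline costs, whatever imbalance is observed.
3. As a clarification, state the resampling unit. The bootstrap should respect the GP clusters and keep each patient's cost and QALY together. Because there are only about 12 GPs per arm, add a small-sample correction or a coverage check, since simple resampling of whole GPs also gives intervals that are somewhat too narrow.

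The cost is plan wording and analysis code. The profile is already collected at all four visits, so no new data are needed. The baseline cost questionnaire has a 4-week recall, and baseline costs would enter as a covariate on that basis. Adjustment should improve precision where baseline predicts follow-up. Respecting clusters would widen the intervals somewhat if patients would otherwise have been resampled.

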### Randomization and statistical analysis

To prevent a crossover effect between the interventions, cluster-randomization will be performed with the GP as the unit of clustering. A senior academic statistician will produce the randomization schedule based on a stratified block randomization. Stratification variables consist of region (north, central and east Netherlands) and type of practice (single versus group practice). This schedule will be send in a protected Excel-sheet to a research assistant who will allocate the GP in order of their entry to either intervention or control group. The research assistant will communicate the allocation to the researcher who will, in turn, communicate this to the GP. We are not able to keep the SCID interviewer blind to the patient’s condition. The clinical outcome data will be analysed and reported according to the CONSORT guidelines, i.e. both on an intention-to-treat and per protocol basis. With regard to missing data, sensitivity analyses will be conducted with different types of imputation. Multilevel analyses will be used to account for the hierarchical structure of the data (i.e. multiple assessments nested within patients, patients nested within GPs, and GPs nested within practices).

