### Sample size

Based upon earlier research we expect a discontinuation rate for patients in the SPD condition of 15% and a 40% discontinuation rate for patients in the SPD + MBCT condition. We used data from Eveleigh [17] to predict discontinuation in the SPD condition (where 6% successful discontinuation was observed according to very strict criteria, and we made adaptations to align with the context of the current setting, e.g. all patients had a clear intention to taper). To estimate the rate in the SPD + MBCT condition, we looked at studies with available data on adherence to tapering after MBCT, ranging between 53 and 71% [23–25]. Again we made a conservative adaptation of 40% to account for differences in time frame (6 versus 15 months), intention-to-treat versus per-protocol sample, and considering the difficulties in discontinuation and withdrawal symptoms as mentioned in the literature [16]. The following assumptions were used in the sample size calculation: power 80%, alpha of 5% and two tailed testing. Due to the fact that the trial will be cluster randomized, the calculated number of patients assuming individual randomization, has to be inflated by a design factor. To account for this an intra-class correlation (ICC) of 0.05 was used, which is commonly used for research including outcome measures [26]. With regard to the mentioned research we also assume a dropout rate of 15%. Taking these figures into account a total of 24 GPs have to be included, with 138 patients participating in the study; including 69 patients per described condition; presenting an estimate of 5 participating patients per GP.

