### Primary analysis

The primary analysis is aimed at comparing the effects of SPD and SPD + MBCT with regard to the proportion of patients who fully discontinue their antidepressant medication within 6 months. Full discontinuation is defined as using 0 mg antidepressant medication before or at the 6-month assessment. Patients who drop out before this assessment will be classified as ‘not able to discontinue’ (for the primary outcome variable). However sensitivity analyses will be conducted to examine different types of imputation. We will use a multilevel logistic regression model for repeated measures to analyze differences between the two conditions on baseline, 6 months, 9 months and 12 months follow-up measurements.

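### GP randomisation is stratified by region and practice type, but no stated model includes either factor; if they are prognostic, the analysis is mildly conservative (minor)

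*Protocol article*

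**What the plan says.** The section on randomization and statistical analysis describes stratified block randomisation with the GP as the unit: "Stratification variables consist of region (north, central and east Netherlands) and type of practice (single versus group practice"). That makes 3 x 2 = 6 strata. The same section sets out a multilevel structure with levels for assessment, patient, GP and practice.

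Under Primary analysis the article says "We will use a multilevel logistic regression model for repeated measures" and names no covariate. Under Secondary analyses it specifies Cox regression for relapse and multilevel regression for the other outcomes, and gives one covariate rule: "Baseline scores of all continuous variables will be included as covariates in the respective analyses". Region and practice type are categorical design factors, so this rule does not reach them. No other sentence on the clinical models mentions them.

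**The concern.** Both stratification factors are properties of the GP's practice. If discontinuation rates differ by region or practice type, stratified allocation spreads those differences evenly over the arms, so they add little to the real variability of the treatment estimate. A model without the factors leaves the same differences in the GP or practice random effect and charges them to the standard error of a treatment effect that is itself estimated between GPs. The random effects do not cure this: they treat region and practice type as unexplained cluster variation.

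The reported standard error would then be larger than the true one, the test would reject too seldom under the null, and some of the benefit of stratifying would be lost. The trial plans for 80% power with 24 GPs, so it has little precision to spare. Naming the factors in advance also removes a modelling choice that could otherwise be made after the data are seen.

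**Working it through.** **Inputs from the Sample size section.** Discontinuation 15% (SPD) and 40% (SPD + MBCT); "power 80%, alpha of 5% and two tailed testing"; "an intra-class correlation (ICC) of 0.05 was used"; dropout 15%; 5 patients per GP; 24 GPs; 138 patients, 69 per arm.

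**Reproducing the stated sample size.** Two proportions, pooled variance, no continuity correction, mean proportion 0.275:

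- n = [1.96 x sqrt(2 x 0.275 x 0.725) + 0.842 x sqrt(0.15 x 0.85 + 0.40 x 0.60)]^2 / 0.25^2 = 48.9, so 49 per arm.
- Design effect 1 + (5 - 1) x 0.05 = 1.20; 49 x 1.20 = 58.8.
- Dropout: 58.8 / 0.85 = 69.2 per arm, against 69 stated.

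The plan's figure reproduces. After dropout, 138 x 0.85 = 117 patients remain, about 4.9 per GP.

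**Assumption not in the documents.** Let f be the share of between-GP variance that region and practice type explain. The article gives no information on f, so it is shown over a range that includes zero. The strata are taken as balanced between arms.

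**Formulas.** The unadjusted model reports a variance proportional to 1.20. The true variance under balanced strata is proportional to

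- short form: D = 1 + 4 x 0.05 x (1 - f);
- fuller form, which takes the explained share out of the whole between-GP component: D = 0.95 + 5 x 0.05 x (1 - f).

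The reported SE is too wide by the factor r = sqrt(1.20 / D). The actual two-sided error rate of the nominal 5% test is 2 x [1 - Phi(1.96 x r)].

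| f | D, short | r, short | Actual error rate, short | D, fuller | r, fuller |
|---|---|---|---|---|---|
| 0 | 1.20 | 1.00 | 5.0% | 1.20 | 1.00 |
| 0.25 | 1.15 | 1.02 | 4.5% | 1.1375 | 1.03 |
| 0.50 | 1.10 | 1.04 | 4.1% | 1.075 | 1.06 |
| 0.75 | 1.05 | 1.07 | 3.6% | 1.0125 | 1.09 |

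**Power, short form.** With normal critical values, unadjusted and adjusted power are 80.0% and 80.0% at f = 0, 80.5% and 81.7% at 0.25, 81.0% and 83.4% at 0.50, and 81.6% and 85.1% at 0.75. Adjustment uses three parameters, so between-GP degrees of freedom fall from 24 - 2 = 22 to 24 - 5 = 19. With t critical values, the change in power from adjusting is about -0.6, +0.7, +2.0 and +3.4 points. These move by a few tenths with the approximation used.

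**Cost if the factors do not matter.** The ratio of t critical values is 2.093 / 2.074 = 1.009, so intervals are about 1% wider.

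**Simulation check.** A random-intercept logistic model was fitted with and without the two factors: 24 GPs x 5 patients, a single 6-month outcome, 500 runs per setting, normal critical values.

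| f | Null rejection, unadjusted | Null rejection, adjusted | Power, unadjusted | Power, adjusted |
|---|---|---|---|---|
| 0 | 4.6% | 4.8% | 0.784 | 0.816 |
| 0.5 | 3.8% | 4.4% | 0.80 | 0.83 |
| 1 | 3.2% | 5.6% | 0.848 | 0.896 |

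Monte Carlo error is about 1 point on the null rates and 1.5 to 2 points on power. The unadjusted null rate falls as f rises, as the formulas predict. The power columns should not be used for size. The apparent gain of 3.2 points at f = 0 cannot be real precision, because the empirical SD of the estimate rose from 0.524 to 0.531 while the mean reported SE fell from 0.512 to 0.498. The size given here therefore rests on the closed-form figures with t critical values.

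**The case against.** The strongest reply is that this is silence in a condensed article. The covariate rule does not say that baseline scores are the only covariates, the primary model is not fully specified, and an analysis plan not at hand may include the strata. This largely stands. A reader might infer that the trial has decided against adjustment, and the text does not support that. It supports only that the models as stated omit the factors. But the article does give model types, nesting levels and a covariate rule, and an analyst who followed them would fit an analysis that does not match the randomisation.

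The second reply is that the harm needs prognostic strata. This also stands. The article gives no reason for choosing the factors and no data on their relation to discontinuation. Region may be there for logistical reasons, since recruitment is organised by region. At f = 0 nothing is lost, and adjustment costs slightly.

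A reader might also infer that 24 GPs in six strata must leave incomplete blocks and uncorrected imbalance. No block size is stated, so that is not shown. It would also work against the main argument, because imbalance between arms means that stratification removed less variance and the excess in the standard error is smaller.

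Finally, the calculation covers one binary comparison at 6 months. It shows no loss for the Cox model or the cost model.

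**Conclusion.** The point holds as a minor improvement. The stated models leave out the two factors used to stratify the randomisation, and the GP and practice random effects do not replace them. Under an ICC of 0.05, about 5 patients per GP, balanced strata and f between 0 and 0.75, the unadjusted SE is 0% to about 7% too wide (about 9% under the fuller formula). The nominal 5% test runs at 5% to about 3.6%, and adjustment changes power by about -0.6 to +3.4 points.

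A reader might take the mismatch between design and analysis to mean a raised false-positive rate or an invalid primary test. It means neither: the error is on the conservative side. The planned sample size reproduces and does not need to change. How large the loss is in this trial cannot be settled from the article, because it depends on how prognostic the strata are.

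**What to change.** State that region (two indicators) and practice type (one indicator) enter as prespecified fixed main effects in the primary multilevel logistic model and in the secondary multilevel regression models, alongside the baseline scores already planned. Main effects (3 degrees of freedom) are safer than all six strata (5 degrees of freedom) with 24 GPs.

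The cost is one sentence. Both factors are already known for every GP at randomisation, so no new data and no extra patients are needed. The statistical price is 3 of about 22 between-GP degrees of freedom. If an existing analysis plan already includes the factors, a line saying so closes the point.
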